### Measurement of outcomes

#### Delirium assessments

Trained investigators who are blinded to the group assignment will assess the development of POD using CAM for the Intensive Care Unit (CAM-ICU) and 3-min diagnostic interview for CAM (3D-CAM) for ICU patients and ward patients, respectively. The assessment will be conducted twice a day from the postoperative day 1 until the postoperative day 5 (or discharge whichever comes first) in the morning and the evening, with at least six hours elapsing between assessments. On the day of surgery, delirium assessment will be conducted at least 2 h after the end of surgery. Delirium will be assessed when patients can be aroused sufficiently (Richmond Agitation-Sedation Scale [RASS] >  − 4) (Scale 2003). 3D-CAM is highly sensitive and specific for delirium in hospitalized patients (Marcantonio et al. 2014) and the CAM-ICU is a well-validated method of delirium assessment in intubated patients or in the ICU (Ely et al. 2001). In addition, we adopted structured chart reviews to prevent missing cases during the night shift to detect episodes of delirium (Inouye et al. 2005; Saczynski et al. 2014). This approach increases the sensitivity while maintaining specificity in detecting the incidence of delirium. The severity of POD will be evaluated using the maximum daily score of the Delirium Rating Scale-Revised (DRS-R-98), 0 (no delirium) to 39 (highest severity of delirium) for patients who are screened positive for delirium based on the 3D-CAM or CAM-ICU.

The type of POD will be classified into 3 subtypes (Peterson et al. 2006), which are hyperactive (with a consistently positive RASS, from + 1 to + 4), hypoactive (with a consistently neutral or negative RASS, from 0 to − 3) and mixed type. The severity of delirium will be assessed in the patients who develop delirium within 5 days using the DRS-R-98 and maximum DRS is used in the analysis, 0 (no delirium) to 39 (highest severity of delirium).

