### Outcomes

#### Primary outcome

The primary outcome is the incidence of POD as defined by any positive assessment between 2 h after surgery and postoperative day 5 or discharge, whichever comes first.

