#### Secondary outcomes

Secondary outcomes are (1) severity of delirium, (2) number of positive delirium assessment, (3) emergence agitation which is defined as RASS + 1 or more within 30 min after the endotracheal extubation, (4) delayed extubation (> 1 h after surgery), (5) perioperative adverse events including intraoperative awareness with recall or undesirable patient movement, bradycardia with the use of chronotropic agent, laryngeal spasm, bronchospasm, allergic reaction, arrhythmia, cardiac events (myocardial infarction, vasospasm, or cardiac arrest), or massive bleeding, (6) area under the mean blood pressure threshold (AUT), (7) quality of recovery using Qor-15 questionnaire (Stark et al. 2013), (8) postoperative nausea and vomiting (PONV), (9) incidence and severity of non-delirium complications (non-neurologic or neurologic) within 30 days after surgery, which are graded using Clavien-Dindo classification (Dindo et al. 2004; Landriel Ibañez et al. 2011), (10) length of hospital, defined as the number of days from index neurovascular surgery until initial hospital discharge and ICU stay, defined as the number of hours in the neurosurgical ICU following index neurovascular surgery until the initial ICU discharge, (11) changes in cognition. (12) The occurrence of fall-down and associated injury and functionality at 3 months after surgery.

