### Statistical analysis

All reported study results except adverse events and non-delirium complications are analyzed, following the modified intention-to-treat-principle (ITT). Data will be descriptively presented using summary statistics such as median and quartiles, means and SD, or frequency and percent as appropriate. The standardized mean difference (SMD) will be used for the comparison of baseline data between the randomized groups. Acceptable covariate balance is defined as a standardized mean difference < 0.2 for the entire list of covariates. Repeated measurements, such as NRS score for pain and sleep quality, daily cumulative opioid requirement, and cognitive function will be compared using generalized estimating equation (GEE) analysis among groups.

For the analysis of primary outcome, we will employ a modified ITT principle, which means all randomized participants, regardless of protocol adherence will be included in the primary analysis, except for the case with surgery cancelation and withdrawal of consent after randomization. The incidence among groups will be compared by calculating the 95% CI of the incidence difference: incidence (remimazolam group)-incidence (propofol group), and noninferiority will be achieved if the upper limit of 95% CI is < 10%. The incidence of POD will be compared using a one-sided two-sample *z*-test with an alpha level of 0.025. We will use a multivariable logistic regression model, which will adjust the treatment effect for covariates found to be imbalanced between the two groups.

For the secondary outcome, except for the analysis of intraoperative adverse events and non-delirium complications in which the PP approach will be used, a modified ITT approach will be used. Group comparison will be performed using a two-sample *t* test or Mann–Whitney *U* test as appropriate for continuous variables, and a chi-square test or Fisher’s exact test for categorical variables. We will adjust the effect of imbalanced covariates using a multivariable logistic regression model for count variables and linear regression or quantile regression for continuous variables.

Subgroup analyses will be conducted to assess the consistency of differences in the primary outcome used to differentiate the effect of treatment among different populations (age, sex, surgery type, preoperative cognitive impairment, ASA physical status, duration of anesthesia, alcohol abuse, or preoperative benzodiazepine use within 24 h).

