A one-sided *P* value < 0.025 for the primary endpoint and a two-sided *P* value < 0.05 for the secondary endpoints will be considered statistically significant. Missing data will not be replaced, and interim analysis will not be performed. All statistical analyses will be performed by statistical experts utilizing SPSS, SAS, or R software.

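### Delirium severity is scored only in patients with delirium, and the plan does not say that the others enter the severity analysis as 0

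*Protocol article*

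**What the plan says.** Severity is the first item in the list of secondary outcomes: "Secondary outcomes are (1) severity of delirium, (2) number of positive delirium assessment".

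The Delirium assessments section restricts scoring twice. Its first paragraph has the DRS-R-98 scored "for patients who are screened positive for delirium based on the 3D-CAM or CAM-ICU". Its second paragraph says "The severity of delirium will be assessed in the patients who develop delirium within 5 days using the DRS-R-98", and adds that "maximum DRS is used in the analysis, 0 (no delirium) to 39 (highest severity of delirium".

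The patients so selected are essentially those who meet the primary outcome, which is "the incidence of POD as defined by any positive assessment between 2 h after surgery and postoperative day 5 or discharge, whichever comes first".

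Three statements in the Statistical analysis section bear on how the scores are used:
- For secondary outcomes, apart from intraoperative adverse events and non-delirium complications "in which the PP approach will be used, a modified ITT approach will be used".
- Continuous variables are compared by t test or Mann–Whitney test.
- "Missing data will not be replaced, and interim analysis will not be performed".

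The Delirium assessments section also uses structured chart review to pick up episodes that the scheduled assessments miss.

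**The concern.** Two sets of statements point to different analysis populations. The scoring rule, with no replacement of missing data, leaves a severity value only for patients with delirium. The 0 anchor and the modified ITT rule suggest that everyone belongs in the comparison. The article does not say which applies.

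If the scoring rule decides, the test is run in a subgroup formed after randomization by an event that treatment may change. The Background gives reasons for a change in either direction: fewer cases through less hypotension, or more because the drug is a benzodiazepine. Once the drug changes who becomes delirious, the delirious patients in the two arms are no longer comparable by design. A drug that adds mild cases lowers the average severity among its cases while raising the total burden. A significantly lower severity could then be reported, at two-sided 0.05, beside a non-inferiority result.

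**Working it through.** **Inputs from the protocol article (Sample size).** Expected incidence 31.1%, margin 10 percentage points, one-sided alpha 2.5%, power 80%, 330 evaluable per group.

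**The plan's own figure.** The article gives no number for severity, so the only figure to reproduce is the group size:
- n = (1.960 + 0.842)² × 2p(1 − p)/0.10². With p = 0.311 this is 336.4, so 337 against the stated 330, a gap of 2.1%. With p = 0.30 it is 329.7, so 330.
- 330/0.95 = 347.4, so 348 per group as stated.

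The 330 serves here only as the number per arm.

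**Patients with a score.** 330 × 0.311 = 103 per arm. The other 68.9% have none unless 0 is assigned.

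**Direction of the two comparisons.** Let p be the propofol incidence with mean maximum score M. Suppose remimazolam keeps those cases unchanged and adds a proportion a of cases with mean m. The differences, remimazolam minus propofol, are:
- Cases only: (pM + am)/(p + a) − M = a(m − M)/(p + a), negative whenever m < M.
- All patients, 0 for no delirium: (pM + am) − pM = am, positive whenever m > 0.

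The signs therefore oppose each other whenever the added cases are milder than the usual ones but score above 0. If m = M, the cases-only difference is zero. If m > M, it counts against remimazolam.

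**Sizes.** The values of M and m are assumptions, because the article gives no DRS-R-98 scores.

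| Added cases (points) | M, m | Cases-only means: remimazolam vs propofol | Difference | All-patient means: remimazolam vs propofol | Difference |
|---|---|---|---|---|---|
| 3 | 20, 12 | 19.30 vs 20 | −0.70 | 6.58 vs 6.22 | +0.36 |
| 3 | 20, 15 | 19.56 vs 20 | −0.44 | 6.67 vs 6.22 | +0.45 |
| 3 | 18, 14 | 17.65 vs 18 | −0.35 | 6.02 vs 5.60 | +0.42 |
| 5 | 20, 12 | 18.89 vs 20 | −1.11 | 6.82 vs 6.22 | +0.60 |
| 5 | 20, 15 | 19.31 vs 20 | −0.69 | 6.97 vs 6.22 | +0.75 |
| 5 | 18, 14 | 17.45 vs 18 | −0.55 | 6.30 vs 5.60 | +0.70 |
| 10 | 20, 12 | 18.05 vs 20 | −1.95 | 7.42 vs 6.22 | +1.20 |
| 10 | 20, 15 | 18.78 vs 20 | −1.22 | 7.72 vs 6.22 | +1.50 |
| 10 | 18, 14 | 17.03 vs 18 | −0.97 | 7.00 vs 5.60 | +1.40 |

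**How often the cases-only test would mislead.** Simulation of 4,000 trials with 330 per arm and M = 20; assumed SDs are 5 for usual and 3 for added cases. The Mann–Whitney test among cases significantly favours remimazolam in:
- about 2.5% to 2.9% of trials with no added cases;
- 15.7% (m = 12) or 10.9% (m = 15) with 3 added points;
- 30.2% or 18.6% with 5 added points;
- 76.9% or 49.3% with 9.9 added points.

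With any of these added cases, the all-patient test significantly favours remimazolam in at most 0.5% of trials.

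**What the primary result would show in the same scenarios.** SE = √{[p(1 − p) + (p + a)(1 − p − a)]/330}, expected upper limit = a + 1.96 × SE, and the chance of showing non-inferiority is Φ[(10 − a)/SE − 1.96], in percentage points:
- a = 3: SE 3.65, upper limit 10.1, chance about 48%.
- a = 5: SE 3.67, upper limit 12.2, chance about 27%.
- a = 10: SE 3.72, upper limit 17.3, chance about 2.5%.

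**The case against.** A reader might infer that the plan has fixed a cases-only comparison. The article does not go that far. It says in whom severity is assessed, not that the comparison between arms is confined to them. A cases-only analysis has no use for a value meaning no delirium, yet the sentence naming the analysis variable includes one. With the modified ITT rule, the text can be read as scoring the positives, giving the rest 0 and analysing everyone. The full protocol or an analysis plan, neither of which is shown, may say so. This stands, and it limits the point to an unresolved conflict. It does not remove it, because nothing in the article assigns the 0, while the scoring restriction and the missing-data rule, taken literally, lead to the cases-only test.

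The harm is also bounded. Each added case counts in the primary outcome reported alongside, and the number of positive assessments is another secondary outcome. Nothing in the article supports the assumption that added cases would be milder. Being listed first carries no weight, since no hierarchy among secondary outcomes is stated. All of this stands.

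Finally, with about 69% of patients tied at 0, an all-patient rank test partly repeats the incidence comparison and does not answer how severe delirium is when it occurs. That is a real cost, and a reason to keep the cases-only description beside it.

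**Conclusion.** The point holds as a gap between the scoring rule and the stated analysis principle for one secondary outcome. Followed literally, the severity test conditions on the primary outcome, is not protected by randomization, and can favour remimazolam when the drug adds milder cases. The reversal of sign is general under that condition. Its size (0.35 to 1.95 points lower among cases, 0.36 to 1.5 points higher overall) depends entirely on assumed DRS-R-98 means, and the simulated percentages also depend on assumed SDs.

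A reader might infer that a favourable severity result could hide a large excess of delirium. The documents do not support that: at 10 added points non-inferiority would be shown only about 2.5% of the time, and the excess would be visible in the incidence. The combination is more plausible for small excesses. At 3 added points non-inferiority is close to a coin toss, and the cases-only test favours remimazolam in about 11% to 16% of simulated trials.

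This is a minor-to-moderate point. The primary test, the margin and the sample size are unaffected.

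**What to change.** State the following in the analysis plan before unblinding:
- Maximum DRS-R-98 is compared across the modified ITT set, with 0 for patients without delirium, by a rank-based method (Mann–Whitney with its probability estimate) or a proportional-odds model.
- A delirium case found only by chart review and lacking a DRS-R-98 score has missing severity and is not set to 0. A sensitivity analysis covers these cases.
- Severity and subtypes among cases only are shown as description, beside the all-patient comparison.

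The cost is a few sentences and one small sensitivity analysis, with no new patient assessments. The price in interpretation is the partial overlap with the incidence result, which the cases-only description offsets.

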#### Cognitive function test

Cognitive assessment will be conducted using Montreal Cognitive Assessment (MoCA) at baseline, 7 days after surgery or at discharge whichever comes first, and 3 months after surgery. Mini-mental state examination is the most widely used cognitive assessment tool for screening and diagnosing dementia; however, it lacks the sensitivity and specificity to detect subtle cognitive impairment (Needham et al. 2017). Therefore, we will use MoCA to detect minimal cognitive impairment (Nasreddine et al. 2005). It comprises six domains: Memory; Executive Functioning; Attention; Language; Visuospatial; and Orientation. Three months later, a telephone interview for the cognitive change will be performed using T-MoCA (Pendlebury et al. 2013), which omits visuospatial, executive, and memory functioning from the MoCA test. The occurrence of fall-down and associated injury and functionality using the Barthel ADL index within 3 months will be assessed using telephone interviews.

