**Fig. 1 Fig1:**
[figure not shown]
The Consolidated Standards of Reporting Trials flow diagram

**Table 1 Tab1:** Overall schedule of participants

Timeline	Enrollment	Allocation	Post-allocation							
Timepoint	Within 72 h of admission	Surgery day	*Postoperative day*							
			*0*	*1*	*2*	*3*	*4*	*5*	*7*	*90*
Enrollment:										
Eligibility screen	X									
Informed consent	X									
Allocation		X								
Interventions:										
Propofol group		X								
Remimazolam group		X								
Assessments:										
Baseline variables	X									
Frailty, fall-down, and functionality assessment	X									X
Cognitive assessment (MoCA)	X								X*	X
Intraoperative data		X	X							
Intraoperative adverse events		﻿X	﻿X							
Delirium assessment (CAM-ICU, 3D-CAM)	X		X	X	X	X	X	X		
Quality of recovery				X						
Pain score and opioid requirement			X	X	X	X	X			
Postoperative neurologic and non-neurologic complications			X	X	X	X	X	X	X	X

^*^If the patient is discharged before POD 7, it is performed before discharge

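### Cognition is measured with full MoCA up to day 7 and a shortened telephone T-MoCA at 3 months, so a raw 3-month change or a visit-averaged GEE effect mixes two scales

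*Protocol article*

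**What the plan says.** All places are in the protocol article.

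- **Cognitive function test** first assigns MoCA to three visits: "at baseline, 7 days after surgery or at discharge whichever comes first, and 3 months after surgery". It describes the test thus: "It comprises six domains: Memory; Executive Functioning; Attention; Language; Visuospatial; and Orientation".
- The same paragraph then changes the instrument at the last visit: "a telephone interview for the cognitive change will be performed using T-MoCA", a version "which omits visuospatial, executive, and memory functioning from the MoCA test".
- **Table 1** has a single row, "Cognitive assessment (MoCA"), marked at enrollment, day 7 and day 90. T-MoCA does not appear in the table.
- **Secondary outcomes**, item 11, is "changes in cognition", with no further definition.
- **Statistical analysis** lists cognition with pain, sleep quality and opioid use as repeated measurements: "cognitive function will be compared using generalized estimating equation (GEE) analysis among groups". It does not separate the visits by instrument.

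The article states no shared-item score, conversion or rescaling between the two tests, and no separate analysis for 3 months.

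**The concern.** A change score, or a repeated-measures model for a mean, needs the same quantity at every visit. Here the first two visits give a six-domain score and the last gives a score that, by the protocol's description, lacks three of those domains. Subtracting baseline from the 3-month score adds the effect of the shorter test to any change in the patient. A single treatment effect averaged over day 7 and 3 months combines differences on two scales, and its size depends on which domains the drug affects.

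This is more than an omitted detail. The article states the switch of instrument, says that the 3-month interview is for cognitive change, and names a repeated-measures analysis. Followed as written, these do not fit together. It also gives two answers to which test is used at 3 months. The outcome has some weight: the Background cites long-lasting cognitive dysfunction as a reason why delirium matters, and MoCA was chosen for its sensitivity to mild impairment.

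**Working it through.** The protocol gives no figure for the cognition outcome, so there is none to reproduce. The sample size concerns delirium and plays no part here.

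**1. Content by visit (from Cognitive function test)**

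| Visit | Test | Domains |
|---|---|---|
| Baseline | MoCA | 6 |
| Day 7 or discharge | MoCA | 6 |
| 3 months | T-MoCA | 6 − 3 = 3 (attention, language, orientation) |

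Baseline to day 7 is on one scale. Any comparison of 3 months with an earlier visit is not.

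**2. Size of the artefact in a raw change**

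The documents give no score maxima, so these inputs are assumptions: full score 100, mean 80% correct in all domains, no true change, and T-MoCA keeping a share *s* of the points.

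Apparent mean change = 80*s* − 80 = −80(1 − *s*).

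| *s* | Apparent change |
|---|---|
| 0.40 | −48 |
| 0.50 | −40 |
| 0.60 | −32 |
| 0.75 | −20 |

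**3. Dependence on baseline**

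Further assumptions: between-patient SD of 10 points and measurement SD of 3 points at each visit, on the 100-point scale. Then

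corr(change, baseline) = −[100(1 − *s*) + 9] / √{[100(1 − *s*)² + 18] × 109}.

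- *s* = 0.40: −69/√(54 × 109) = −0.90
- *s* = 0.75: −34/√(24.25 × 109) = −0.66
- *s* = 1 (same test twice): −9/√(18 × 109) = −0.20

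So with the shortened test, the raw change largely reflects how high the patient scored at baseline.

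**4. Between-arm contrast**

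Both arms switch at the same visit. With no treatment effect, the difference in mean change is −80(1 − *s*) − [−80(1 − *s*)] = 0. A simulation under the assumptions of steps 2 and 3 gave differences between −0.08 and 0.05 points. The switch alone does not bias the randomised comparison at 3 months.

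**5. Effect averaged over visits**

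Suppose that the true effect on the full scale is *d* at both day 7 and 3 months, and that a share *f* of it lies in the retained domains. The raw 3-month effect is *f·d*, and the equally weighted average is *d*(1 + *f*)/2. This runs from *d*/2 (*f* = 0) to *d* (*f* = 1). The averaged effect thus has no fixed meaning, although it is still zero when the drug has no effect.

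**The case against.** The strongest reply is that the planned comparison is between arms and that the article does not specify the GEE. If visit is a factor and treatment effects are visit-specific, the common shift goes into the visit effect and the 3-month contrast stands. That is correct and limits the point. It does not rescue a raw change from baseline or a visit-averaged effect, and the article states no visit-specific terms.

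A second reply is that scoring belongs in the full protocol or in the analysis plan to which Data management refers. An unseen document may indeed define a common score. The article is still inconsistent about the 3-month instrument, and it names one analysis for measurements that are not on one scale.

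A third is that the Table 1 label is shorthand, since the text names T-MoCA openly. That is fair for the table alone, where a small correction suffices.

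A reader might infer more than the documents support:

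- **That every patient will appear to decline, or will cross a threshold for decline.** The first needs raw subtraction, which is not stated. No threshold or decline rate appears in the article.
- **That the whole cognition outcome is uninterpretable.** Baseline to day 7 is on one test, and three domains are still measured at 3 months.
- **That between-arm effects must be compressed at 3 months.** Step 5 shows that this depends on which domains are affected.

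Whether the article describes the content of T-MoCA correctly cannot be checked from the documents.

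**Conclusion.** The point holds in limited form. A raw baseline-to-3-month change, or a treatment effect averaged over day 7 and 3 months, mixes two scales with different content and cannot be read as change in cognition. Under the assumptions of step 2, the artefact in the raw change is 20 to 48 points out of 100, the same in each arm. That range illustrates scale and is not an estimate for this trial.

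The baseline-to-day-7 change is unaffected. A between-arm comparison at 3 months alone is not biased by the switch, but it cannot show effects in the domains that T-MoCA leaves out. This is one of twelve listed secondary outcomes, and the primary delirium analysis and its sample size are untouched. It should be corrected, but it does not threaten the trial's main conclusion.

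**What to change.** Before group allocation is opened:

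1. Analyse the change from baseline to day 7 or discharge on the full MoCA.
2. For 3 months, re-score baseline and day 7 on the items shared with T-MoCA, and analyse that common score across visits.
3. If item-level scores have not been kept, analyse 3-month T-MoCA as a separate between-arm endpoint adjusted for baseline MoCA, and do not call it a change.
4. Do not enter raw MoCA and raw T-MoCA totals in the same GEE.
5. Name T-MoCA at day 90 in Table 1 and in the opening sentence of Cognitive function test.

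**Cost.** Where item scores exist, the change needs re-scoring and wording but no new data. The article mentions only a predetermined case report form, so whether items are recorded must be checked. The common score covers fewer domains, and it does not remove any difference between telephone and in-person testing.

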### Safety monitoring

As the administration and dosage of study medications in both anesthesia regimens are within the current clinical practice, we believe that SAEs should be rare. The adverse effects of propofol and remimazolam will be closely monitored during operation by attending anesthesiologists. In case of fetal adverse events, they could stop the infusion of study medications, request the unmaking of group allocation, and inform the principal investigator of any reason for stopping the infusion of study drugs. In addition, a designated investigator will review the occurrence of adverse events possibly caused by study drugs from the start to the end of infusion using chart review. The DMC will perform a review to ensure patient safety. Throughout the study, any adverse events should be reported within 24 h to the DMC.

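### After surgery, falls are scheduled to be ascertained only by the 3-month telephone interview, so in-hospital falls may be under-recorded for secondary outcome 12

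*Protocol article*

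**What the plan says.** Secondary outcome 12 in the protocol article is "The occurrence of fall-down and associated injury and functionality at 3 months after surgery". The section Cognitive function test names the source and the window: "The occurrence of fall-down and associated injury and functionality using the Barthel ADL index within 3 months will be assessed using telephone interviews". Read together, the outcome covers the three months after surgery and its source is a telephone interview.

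In Table 1, the row "Frailty, fall-down, and functionality assessment" has two marks, one at enrollment and one at day 90. Days 0 to 5 and day 7 are blank. The enrollment mark is a baseline assessment.

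The hospital record is already read for another outcome. Under Delirium assessments the article says: "In addition, we adopted structured chart reviews to prevent missing cases during the night shift to detect episodes of delirium". It adds that this raises sensitivity without loss of specificity.

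**The concern.** A fall on the ICU or ward in the first days after surgery reaches outcome 12 only if it is reported in an interview about three months later. A patient who was delirious at the time may be less able to report it. Losses of this kind would be related to delirium, which is the primary outcome and may differ between the arms.

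At stake is how complete and how comparable a safety-relevant secondary outcome is. A more reliable source for the in-hospital part, the medical record, is already being read for delirium.

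**Working it through.** **Step 1. Could any other stated route supply in-hospital falls to outcome 12?** The plan gives no figure for falls, so there is none to reproduce. The check is first one of coverage.

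| Route | Section | Reaches in-hospital falls for outcome 12? |
|---|---|---|
| Telephone interview | Cognitive function test; Table 1, day 90 | Yes, but only as a late report |
| Structured chart review | Delirium assessments | Stated purpose is delirium episodes; falls not named |
| Chart review for adverse events: "review the occurrence of adverse events possibly caused by study drugs from the start to the end of infusion using chart review" | Safety monitoring | No; it ends with the infusion, before ward falls occur |
| Row "Postoperative neurologic and non-neurologic complications", days 0 to 5, 7 and 90 | Table 1 | Could record a fall with injury; falls not named, not linked to outcome 12 |
| "Throughout the study, any adverse events should be reported within 24 h to the DMC" | Safety monitoring | Could record a fall; falls not named, not linked to outcome 12 |

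Only the interview is assigned to the outcome.

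**Step 2. Does the protocol itself give reason to doubt late self-report?** In part.
- Background cites a close relation between delirium and long-lasting cognitive dysfunction.
- Under Adverse events, the awareness questionnaire is postponed in delirious patients until the delirium has resolved. Postponing does not help with a fall that was never remembered.
- The telephone cognitive test at 3 months omits memory, so that test does not show whose recall is weak.

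**Step 3. What does under-recall do to the comparison?** Let p be the true fall risk in an arm and s the share of falls reported. The recorded risk is s × p.
- Equal s in both arms: the recorded risk ratio equals the true one, and the risk difference shrinks by the factor s. With assumed risks of 5% and 10% and s = 0.8, the recorded risks are 4% and 8%. The ratio stays at 2 and the difference falls from 5 to 4 points.
- Unequal s: with the same risks and s = 0.8 and 0.6, the recorded risks are 4% and 6%, a ratio of 1.5. Only at 0.8 and 0.4 do they meet, at 4% and 4%.

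**Step 4. How unequal would recall be if it depended on delirium alone?** From Sample size, take the 31.1% delirium rate for one arm and add the 10-point margin for the other, giving 41.1%. Assume fall risks of 4% without and 12% with delirium. These two risks and the recall values below are assumptions, since the documents give none.

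True risks:
- 0.311 × 12% + 0.689 × 4% = 6.49%
- 0.411 × 12% + 0.589 × 4% = 7.29%
- difference 0.10 × (12 − 4) = 0.80 points; ratio 7.29/6.49 = 1.12

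If r_D and r_N are recall with and without delirium, the recorded difference is 0.10 × (12 r_D − 4 r_N) points.

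| r_N | r_D | Recorded risks | Difference (points) | Ratio | Average recall by arm |
|---|---|---|---|---|---|
| 0.8 | 0.8 | 5.19% and 5.83% | 0.10 × (9.6 − 3.2) = 0.64 | 1.12 | 80% and 80% |
| 0.8 | 0.6 | 4.44% and 4.84% | 0.10 × (7.2 − 3.2) = 0.40 | 1.09 | 68% and 66% |
| 0.8 | 0.4 | 3.70% and 3.86% | 0.10 × (4.8 − 3.2) = 0.16 | 1.04 | 57% and 53% |

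The direction is dilution. The gap in average recall between arms is only about 2 to 4 points, even at a delirium difference equal to the full margin. The table applies the recall loss to all 90-day falls. The share that happens in hospital is not given, so the part a chart source would recover is unknown.

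**The case against.** The strongest reply has four parts.

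1. **The respondent is not specified.** The article says telephone interviews and does not say who answers. A relative's answer is neither required nor excluded, and the call script may be in the full protocol. This stands. It means that reliance on the patient's own memory is likely but not stated. It does not change the fact that the printed schedule has no in-hospital fall assessment.

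2. **Other routes exist.** A fall with injury could be recorded as a complication or an adverse event. This also stands, so such a fall need not be lost to the trial. Neither route names falls or feeds outcome 12, however, and a minor fall could be missed by both.

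3. **Equal under-recall leaves the risk ratio intact.** Patients and outcome assessors are blinded, and the documents give no evidence that recall differs between arms. This is correct. Blinding prevents differences due to knowing the treatment, though not differences due to delirium. The illustration suggests the latter would be modest.

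4. **Little depends on it.** Falls are part of the last of twelve secondary outcomes, and the sample size was not set for them. This is correct, and it is why the point is minor.

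**Conclusion.** The point holds as a minor improvement. The only scheduled post-operative ascertainment of falls for outcome 12 is the 3-month interview. In-hospital falls may therefore be under-recorded, more so after delirium, and a difference between arms can be diluted. The size is unknown. The figures in the working rest on assumed fall and recall rates and show direction only. Their absolute differences, all below one percentage point, are small. The primary non-inferiority conclusion is unaffected.

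A reader might infer two stronger things, and the documents support neither. The first is that the design conceals a real difference in harm. Full masking needs strongly unequal recall between arms, for example 80% against 40% when true falls double. Nothing in the documents points to that, and a delirium difference at the margin does not produce it in the illustration. The second is that the investigators foresee impaired memory in their patients. They cite a link between delirium and cognitive dysfunction and they measure cognition, but their hypothesis is non-inferiority on delirium and they state no expected memory loss.

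**What to change.** - Take in-hospital falls and associated injuries from the medical record up to discharge. Add the item to the structured chart review already done for delirium, completed by staff blinded to allocation. Delirium follow-up ends at day 5 or discharge, so for patients still in hospital the review must run on to discharge.
- Keep the 3-month call for falls after discharge.
- Define outcome 12 as a fall recorded in either source.
- Mark falls at discharge as well as at day 90 in Table 1.

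The cost is one more item on a slightly longer chart review, with no extra visit. The outcome becomes mixed-source, but in the same way in both arms. Falls after discharge would still depend on the call.
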